## Ethics and dissemination

This study has ethical approval from the Regional Ethical Committee in Sweden (Dnr: 2024-04185-02, 2024-06783-02, 2023-00191-01, 2022-02897-02, 2022-05624-01, 2018/11-31/2). Given that the study is retrospective and register-based, using only pseudonymised data, there are minimal physical, psychological or privacy risks to included individuals. At the time of entering HIV care, PWH are informed about the InfCareHIV registry, after which they can opt-out, which is very rare. They are informed that deidentified data may be used and published for research, given that ethical permission has been granted, and therefore individual consent is not necessary for each individual research project. All results will be presented on population level with no possibility of identification. The long-term risks could include misuse of predictive models if they are not updated with current data or if used to unjustly discriminate against individuals at higher risk. We will advocate for the integration of cancer risk prediction models into routine HIV care, and the ethical ramifications of such new policies will be critically examined. This project is expected to contribute to improved public health outcomes, particularly in CRC prevention and early detection among individuals with HIV. It also aims to inform healthcare policies and potentially reduce healthcare disparities. The beneficiaries of this research include PWH at risk of CRC, healthcare providers and policymakers. The negligible short-term risks are balanced against the substantial long-term value of potentially saving lives through early CRC detection and tailored prevention strategies. Moreover, the research is conducted with patient advocacy and ethical considerations at its core, ensuring that the benefits are maximised while risks are minimised.

### Data storage and security

Pseudonymised register-linkage data are safely stored in a central storage project folder, using Structured Query Language at Karolinska Institutet, Sweden. Only members of the research group can access the data. All data analyses will be performed in the storage folders using a virtual desktop with a two-factor authorisation process. The data will be stored for at least 10 years after the results have been reported and published according to the Swedish Archives Act (1990:782).

### Patient and public involvement

For the planning of this study, we have, since May 2023, involved a patient reference group representing three different HIV patient organisations in Sweden. The reference group is diverse in terms of gender, ethnicity, age and HIV acquisition risk. The research group have regular meetings with the reference group to discuss the aim and design of the study and to ensure that it is aligned with the research questions that the patient organisations have raised as important for the community.

### Clinical relevance

The CRC risk prediction model for PWH will be developed with the aim of supporting risk-stratified CRC surveillance within routine HIV care. The Swedish national CRC screening programme currently invites the general population aged 60–74 years for biennial faecal testing^51^ and does not account for HIV-specific risk factors. A validated risk prediction model could be integrated into the InfCareHIV decision-support interface used at all Swedish HIV clinics, enabling treating physicians at routine annual follow-up to identify individuals who may benefit from earlier screening initiation, shorter screening intervals or referral for colonoscopy. Before clinical deployment, the model will require external validation in independent cohorts and prospective evaluation of its effect on screening uptake, diagnostic yield and stage at diagnosis.

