This study will use comprehensive nationwide data and apply machine learning (ML) methods to develop a CRC risk prediction model. PWoH will be included to increase statistical power. Matching will be used to control for key confounders, and appropriate methods will be applied to minimise bias and prevent overfitting during model development. Sensitivity and subgroup analyses will be conducted to compare model performance across different scenarios. ML-based prediction models may be superior to logistic or Cox proportional hazards (PH) regression-based models. Previous research studies have compared these approaches, resulting in varying conclusions. Some ML methods have been observed to perform as good as, or may be favourable to, Cox PH or logistic regression for some prediction tasks.^8–12^ Logistic or Cox PH regression methods may perform prediction tasks better or worse than some ML approaches,^11^ but data-driven approaches using ML have been favoured in some studies due to their ability to understand complex relationships in data, which may have an advantageous prediction performance.^12^ It may be more difficult to motivate an ML approach in a resource- or time-limited setting, in particular if data quality or dimensionality is lower and Cox PH or logistic regression methods can complete prediction tasks to a comparable level.

This protocol will use an ensemble method called stacking,^13^ which will combine the predictions of multiple ML models to produce an overall predicted risk score of CRC. Each ML method relies on different statistical assumptions and processes that may reflect different patterns in the data and offer unique insights into the relationships between variables and the outcome.^14^ By leveraging the estimates from each model in the ensemble, the perspectives from diverse model approaches can be integrated to create a more robust and accurate prediction.^15–17^ The performance of the ensemble model approach will be compared with the performance of a Cox PH regression model.

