#### Swedish National HIV Register (InfCareHIV)

The InfCareHIV Register includes data on more than 99% of those diagnosed with HIV in Sweden.^7^ When people are diagnosed or when they immigrate to Sweden with an HIV diagnosis, they are informed that their data will be included in the register but that they may opt-out, and that they may opt-out at any time in the future if they are included. InfCareHIV has collected data from all HIV clinics across Sweden since 2003, and earlier data has been retrospectively added.^7^ The register includes demographic variables, such as legal sex and country of birth, as well as variables relating to HIV acquisition such as date of first positive HIV test and the most likely mode of HIV acquisition. At every follow-up visit, routine measures, such as HIV-RNA levels, CD4(+) T cell counts and current ART, are included in the register.

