### Study population

The study population will include all resident PWH and PWoH, 18 years or older, born between 1940 and 2008, who resided in Sweden at any time point between 1983 and 2024. The study period will span from 1 January 1983 to 31 December 2024. The inclusion date will be the day the person turns 18, the start date of residency in Sweden, or the study start date, whichever occurs last. Follow-up will continue until emigration, death, end of study time or until 6 months before the first incident of CRC. The outcome of interest is CRC. See figure 1 for an illustration of the inclusion criteria and how inclusion and the follow-up period were defined.

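### Follow-up starts once, at adulthood, residency or 1983, but the model is aimed at annual HIV visits; no prediction date or horizon links the two

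*Protocol article*

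**What the plan says.** Under Study population, the protocol article gives one start per person: "inclusion date will be the day the person turns 18, the start date of residency in Sweden, or the study start date, whichever occurs last". It then gives one end: "Follow-up will continue until emigration, death, end of study time or until 6 months before the first incident of CRC". The window is fixed ("The study period will span from 1 January 1983 to 31 December 2024"), and so are the birth years ("18 years or older, born between 1940 and 2008"). HIV diagnosis, entry to HIV care and clinic visits do not enter the definition of time zero.

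The section on InfCareHIV describes the HIV predictors as repeated measurements: "At every follow-up visit, routine measures, such as HIV-RNA levels, CD4(+) T cell counts and current ART, are included in the register". The register has collected data since 2003, with earlier data added afterwards.

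Clinical relevance states that the model is developed to support risk-stratified surveillance within routine HIV care. It pictures a decision-support tool "enabling treating physicians at routine annual follow-up to identify individuals who may benefit from earlier screening initiation, shorter screening intervals or referral for colonoscopy". Building it into the clinic interface is worded as a possibility, to follow external validation and prospective evaluation.

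The text names no prediction date and no horizon. It does not say which visit's HIV values enter the models or whether they are updated over time. Data analysis plan refers the variables to online supplemental table 1, which was not available here.

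**The concern.** A physician at an annual visit needs the risk of CRC over the coming years for a person who is in HIV care, CRC-free, of a known age, and has current CD4, viral load and treatment values. The stated design starts the clock at age 18, at arrival in Sweden or on 1 January 1983.

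Two things are at stake. First, the HIV predictors have no value at time zero for anyone diagnosed later, so they must be left out, treated as missing, or taken from a later date. Second, performance measured from the inclusion date says little about performance at a visit many years on. If later values are attached to the earlier origin, performance may also be flattered by information that was not known at the prediction date.

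**Working it through.** The plan gives no figure for this point. Its power statement concerns another question and is not used here. The check is date arithmetic on the plan's own inputs, followed by a reading of how HIV values could enter.

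**Inputs (protocol article).** Birth years 1940–2008; study period 1 January 1983 to 31 December 2024; time zero as defined under Study population; screening ages 60–74 (Clinical relevance); register collection from 2003 (InfCareHIV section).

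**Age at time zero.**
- Resident on 1 January 1983 and born in 1940: 1983 − 1940 = 43, the oldest entry age for anyone resident at the start.
- Residents born from 1965 onward (1983 − 18 = 1965) enter at 18.
- Only later immigrants can enter older than 43.

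**Time from time zero to the start of the screening ages.**
- Resident born in 1940: turns 60 in 2000, and 2000 − 1983 = 17 years.
- Anyone entering at 18: 60 − 18 = 42 years.
- The study period is itself 42 years long. A person turning 18 on its first day turns 60 on 1 January 2025, one day after it ends. Nobody who enters at an 18th birthday is therefore observed at 60.

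**Time from time zero to the HIV register.** 2003 − 1983 = 20 years between the earliest time zero and the start of collection, although earlier data were added later.

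**One constructed case (dates assumed for illustration).** A resident born in 1970 has time zero in 1988. HIV is diagnosed in 2005, and the visit of interest is in 2022 at age 52.
- Time zero to diagnosis: 2005 − 1988 = 17 years with no CD4, HIV-RNA or ART value.
- Time zero to visit: 2022 − 1988 = 34 years.

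**How HIV values could enter, given that time zero.**
1. Fixed at time zero: undefined for everyone diagnosed later. Data preparation drops variables with more than 10% missing. If more than 10% of people with HIV were diagnosed after inclusion, HIV predictors coded this way would fall out even of the substudy restricted to people with HIV.
2. Fixed at a later date or summarised over follow-up (latest or lowest CD4, treatment exposure): defined, but measured after the origin. Their content then depends on how long the person stayed under observation.
3. Time-updated or landmark records: avoids both problems, but the text does not describe it.

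Three details lean towards the second route without proving it. Follow-up stops 6 months before CRC, a gap that makes most sense if predictors are gathered up to the end of follow-up. The train/test split is based on follow-up time, which suggests one follow-up length per person. The only stated safeguard against leakage concerns cluster labels.

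**The case against.** The strongest defence has four parts.

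- **Variable handling is not shown.** A condensed article may leave it to the supplement, and time-updated or landmark records are not ruled out. This stands. A reader might infer that the HIV data are certain to be stale or to leak future information, or that the score cannot be applied validly. The documents do not support either statement as fact. A variable list would not, however, change the inclusion date.
- **A single origin does not by itself prevent prediction from a later age.** With survival function S(t|x), the risk over the next h years for someone event-free at t is 1 − S(t+h|x)/S(t|x). The survival trees are also meant to give probabilities over time, and time-dependent measures are planned. This stands in principle. It leaves open which x is used. On a time-since-inclusion scale it also fails for a person aged 60 who entered at 18, because S beyond 42 years lies outside the data. Using age as the time scale would remove that limit, but the article does not state one.
- **Intended use is conditional.** A reader might take it that the model is to be used at every annual visit. The text says only that a validated model could be integrated, after further study. The aim of supporting surveillance in HIV care is nevertheless stated firmly, and validating the same score from the same origin would not repair the mismatch.
- **The ensemble sentence is not evidence of one lifetime score.** The phrase "which will combine the predictions of multiple ML models to produce an overall predicted risk score of CRC" means combined across learners. This stands, and the point does not rely on it.

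Simulated median gaps of 21–35 years from inclusion to CRC can be produced. They need assumed birth-year distributions, immigrant shares and an age-dependent hazard, none of which are in the documents. They would equal the age of the predictors only if these were frozen at inclusion. They are not used here.

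**Conclusion.** The point holds in a bounded form. The stated time zero ignores HIV diagnosis and visits, the stated purpose is risk assessment in HIV care, and nothing in the text joins them. This goes beyond missing detail, because the inclusion rule as written leaves HIV predictors undefined at time zero for everyone diagnosed after inclusion.

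The size, from the plan's own dates, is 17 years from time zero to age 60 for a resident born in 1940 and 42 years for anyone entering at 18. Later immigrants may enter closer to that age. Whether predictors would in fact be outdated or drawn from after the prediction date depends on coding that is not shown. If visit data are not handled as time-updated or landmark records, the reported accuracy would not describe prediction at a visit. This should be settled before any model is fitted, since changing the origin later means rebuilding every learner.

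**What to change.** Reconcile Study population with Clinical relevance by stating three things:

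1. **Prediction date:** a date in HIV care at which the person is HIV-diagnosed, adult, resident and CRC-free, with the same date assigned to the matched people without HIV.
2. **Predictors:** only values recorded up to that date.
3. **Horizon:** one fixed period (for example 5 years) over which CRC risk is predicted and all models, including the Cox baseline, are evaluated.

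There are two workable forms. Repeated annual landmarks match the intended use most closely. They require each person's records to stay on one side of every train/test and fold boundary, the Time Series Split to be adapted to this, and person-clustered errors. One prediction date per person is simpler.

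**Cost.** No new participants or data sources are needed, but there is more data preparation.
- *Repeated landmarks:* the rows are correlated and more numerous. Assuming about 10 per person, 143,000 × 10 = 1.43 million rows. Pairwise distances for hierarchical clustering grow about 10² = 100-fold.
- *One date per person:* a fixed horizon limits events. Applying the plan's rate of 129.1 per 100,000 to all 13,000 people with HIV (an assumption, with HR 1), 13,000 × 0.001291 × 5 ≈ 84 CRC events over 5 years and ≈ 168 over 10. The horizon should be chosen with that in view.

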### Dissemination plan

All results will be summarised and presented on a population level in meetings with the involved patient organisations. A manuscript with the results of this study will be produced for publication in a peer-reviewed journal. These findings will further be submitted for consideration for oral and poster presentation at conferences. Findings will also be communicated to the Swedish Reference Group for Antiretroviral Treatment and to the European AIDS Clinical Society to inform future revisions of clinical guidance on cancer prevention in PWH.

### Data availability statement

The individual participant data underlying this article were subject to ethical approval and cannot be shared publicly. Data from the deidentified health registries are not freely available due to protection of the personal integrity of the participants. Data are available from CC on reasonable request.
